### Primary endpoint analysis – DILI strategy study

For the analysis of the primary endpoint of the DILI strategy study, the non-parametric Wilcoxon rank sum test will be used for pairwise comparisons. An additional adjusted analysis (with adjustment for the initial randomisation, HIV-status, and the time from initial randomisation to the second randomisation) will be also be performed treating the outcome as an ordinal outcome and using a proportional odds logistic regression model (which can be interpreted as an extension of the Wilcoxon rank sum test).

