## Introduction

### Background

Tuberculous meningitis (TBM) is the most severe form of tuberculosis, resulting in death or neurological disability in approximately 40% of HIV-uninfected sufferers, and 70% of those co-infected with HIV. Effective anti-tuberculosis chemotherapy has been available for more than 50 years, yet tuberculosis kills more people than any other single bacterial infection worldwide. Diagnosing TBM is difficult and depends upon detecting low numbers of
*M. tuberculosis* bacteria in cerebrospinal fluid (CSF). Rifampicin (R), isoniazid (H), pyrazinamide (Z) and ethambutol (E) are the first-line antibiotics for all forms of drug-susceptible tuberculosis. These agents, used daily and in combination, kill the bacteria and prevent the emergence of resistance. There is concern that the blood-brain barrier reduces the concentrations of anti-tuberculosis drugs in the brain which may attenuate both bacterial killing and clinical response
^1^. The most recent Cochrane meta-analysis and systematic review of adjunctive corticosteroids for TBM
^2^ concluded that corticosteroids likely reduced death from TBM in HIV-uninfected individuals in the short term (up to 18 months of follow-up), but had no clear impact on longer term neurological disability or survival.

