### Primary endpoint – DILI strategy study

In the DILI strategy study the primary endpoint is the proportion of time in the 60 days following randomisation during which neither rifampicin nor isoniazid are given (or the subject is dead).

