### Recruitment, retention and randomisation

#### Recruitment and retention

Recruitment activities will only occur in an inpatient hospital setting (Hospital for Tropical Diseases and Pham Ngoc Thach Hospital, Ho Chi Minh City, Vietnam). The target sample size of around 720 participants will be enrolled within an anticipated accrual rate of 4 years. Once discharged from hospital the participants will be contacted by phone to remind them of their next visit. Patients who miss a visit will be contacted by phone for a maximum of three times after which a maximum of three home visits will be conducted. As part of routine clinical care participants with suspected TBM will have an HIV test, a lumbar puncture, and a GeneXpert MTB/RIF test on CSF. When possible, participants will be screened for eligibility on the day their CSF results return and at the time the decision is made to start anti-tuberculosis chemotherapy for suspected/confirmed TBM. For the DILI strategy study, based on enrolment of all consenting and eligible patients, we anticipate a total sample size of 170 participants (around 70 HIV-uninfected participants from the LAST ACT trial and a further 100 patients from the linked ACT HIV trial
^8^.).

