#### Randomisation

Once a participant or their relative has provided written informed consent to enter the study, 5mls of blood will be taken for rapid LTA4H genotyping. The blood will be transported immediately to the OUCRU laboratory within HTD where daily LTA4H genotyping (except at weekends) will be performed. Randomisation will occur once the result of the LTA4H genotyping is available. LTA4H CC- and CT-genotype participants will be randomised to two parallel groups in a 1:1 ratio, receiving either dexamethasone or placebo for 6–8 weeks (according to disease severity). TT-genotype participants will be treated with open-label dexamethasone for 6-8 weeks (according to disease severity). All patients will receive standard anti-tuberculosis chemotherapy. Randomisation will be stratified by participating hospital/site, LTA4H genotype (CC or CT), and modified MRC disease severity grade (
Supplementary File 1) assessed on day 0 when consent is given.

The randomisation list will be computer-generated based on random permuted blocks with variable block size following Oxford University Clinical Research Unit (OUCRU) standard operating procedures. The OUCRU biostatistician in charge of randomisation list preparation will set up statistical code to generate the randomisation list and transfer it to the Study Pharmacist. The Study Pharmacist will then change the random seed, i.e. the initialisation of the random numbers generator, in the statistical code in order to blind the biostatistician and then run the code to prepare the final randomisation list. The generated randomisation lists will be securely incorporated within the trial database. A reliable manual back-up system will also be available. Randomisation to the three strategies for DILI will be 1:1:1 with stratification by initial randomisation (dexamethasone or placebo).

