### Sample size justification – DILI strategy study

A review of 36 subjects who interrupted rifampicin and isoniazid because of clinical hepatitis or jaundice events from our previous trial
^4^ gave the following data: the median (interquartile range (IQR)) onset date of the drug-related liver injury was 50 (15–84) days from initiation of anti-tuberculosis treatment, the median (IQR) duration of the rifampicin and isoniazid interruption was 16 (12–24) days, and 12 subjects subsequently died (8 of them within 60 days). Of note, the duration of the treatment interruption was <t;30 days for 32 (89%) of the 36 subjects and the remaining 4 subjects never re-started rifampicin or isoniazid but continued to receive alternative anti-tuberculosis treatment for >100 days.

We hypothesise that strategies 1 and 2, respectively, will result in a relative reduction in the duration of the treatment interruption of 50% for subjects with interruptions <30 days, but that they do not affect longer interruptions (as the corresponding subject might have permanent intolerance to rifampicin and isoniazid) or mortality. Based on simulations of hypothetical trials using re-sampling from the data described above, the hypothesised treatment effect, and the Wilcoxon rank sum test for analysis, we determined that the power to detect such an effect size with a sample size of at least 50 subjects per arm is >85%. Of note, given this is an ancillary and essentially ‘opportunistic’ study, we have chosen a liberal (i.e. not multiplicity corrected) two-sided significance level of 5% for each of the two primary comparisons of strategies 1 and 2, respectively, versus strategy 3.

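### The primary DILI comparison is a valid but unstratified Wilcoxon test on data pooled from two trials; stratifying by trial (HIV status) and initial arm is a modest, nearly free efficiency gain

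*Protocol article*

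**What the plan says.** All references are to the Protocol article.

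- **Primary test** (Primary endpoint analysis – DILI strategy study): "the non-parametric Wilcoxon rank sum test will be used for pairwise comparisons". No stratification is mentioned. The next sentence adds a proportional-odds analysis "with adjustment for the initial randomisation, HIV-status, and the time from initial randomisation to the second randomisation", and presents that model as an extension of the Wilcoxon test.
- **Endpoint** (Primary endpoint – DILI strategy study): "the proportion of time in the 60 days following randomisation during which neither rifampicin nor isoniazid are given (or the subject is dead"). A death therefore adds every remaining day of the 60 to the score.
- **Who is pooled** (Recruitment and retention): "around 70 HIV-uninfected participants from the LAST ACT trial and a further 100 patients from the linked ACT HIV trial". Design and setting says that the linked trial runs an identical ancillary study and that results will be reported together.
- **Allocation** (Randomisation): "Randomisation to the three strategies for DILI will be 1:1:1 with stratification by initial randomisation (dexamethasone or placebo").
- **Prognosis** (Background): death or neurological disability in "approximately 40% of HIV-uninfected sufferers, and 70% of those co-infected with HIV".
- **Power** (Sample size justification – DILI strategy study): "the power to detect such an effect size with a sample size of at least 50 subjects per arm is >85" per cent, from re-sampling 36 earlier patients and analysing with the Wilcoxon rank sum test.

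**The concern.** A plain rank test compares every patient in one arm with every patient in the other. With a 70:100 mix, the share of between-arm pairs that set an HIV-infected patient against an HIV-uninfected one is 2 × (70/170) × (100/170) = 2 × 0.412 × 0.588 = 48%. If HIV status strongly affects early death, it influences those comparisons and adds noise. A test that compares only within trial and allocation stratum removes that noise.

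The choice also differs from the rest of the article. The main trial's primary Cox model is stratified by MRC grade and genotype, and the disability and rescue-corticosteroid analyses adjust for both. The DILI sample is opportunistic and cannot readily be enlarged, so the choice of analysis is the practical way to gain power.

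**Working it through.** **Inputs from the protocol.** Interruption median 16 days, IQR 12–24; 4 of 36 never restarted; 8 of 36 (22%) died within 60 days. Hypothesised effect: interruptions under 30 days are halved, with no effect on longer ones or on death. Each comparison is two-sided at 5%, with at least 50 per arm (170/3 = 57 expected).

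**Assumptions.** The protocol gives no 60-day mortality or interruption length by HIV status among DILI patients. The 40% and 70% in Background are death or disability in TBM generally and cannot be used as 60-day mortality. HIV-specific values are therefore varied over a range.

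**Method.** 4,000 simulated trials per scenario, from a 36-subject data set rebuilt to the summaries above. Score = days off both drugs before death plus days dead, up to 60. Two tests are compared:

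- plain Wilcoxon: z = (U − E[U]) / √Var(U), corrected for ties;
- van Elteren, stratified by HIV: z = Σ wₖ(Uₖ − E[Uₖ]) / √(Σ wₖ² Var(Uₖ)), with wₖ = 1/(Nₖ + 1), where Nₖ is the number in stratum k over both arms.

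Monte Carlo standard error at 80% power is √(0.8 × 0.2 / 4000) = 0.6 points.

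**Step 1: the plan's own figure.** Single population, 22% mortality, plain Wilcoxon: 88–93% at 50 per arm and 92–96% at 56 per arm. The lower ends arise when all deaths fall in the first 30 days. The stated figure of above 85% is reproduced.

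**Step 2: two HIV strata, 50 per arm (21 HIV-uninfected, 29 HIV-infected), deaths spread over 60 days.** Overall mortality = 0.42 × (HIV–) + 0.58 × (HIV+). The last column is the plain test in a single population with the same overall mortality.

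| Mortality HIV– / HIV+ | Overall | Plain | Stratified | One population, plain |
|---|---|---|---|---|
| 22 / 22% | 22% | 92.5% | 92.3% | 93.0% |
| 15 / 27% | 22% | 93.4% | 93.4% | 93.3% |
| 10 / 31% | 22% | 93.6% | 94.1% | 92.9% |
| 5 / 35% | 22% | 93.0% | 93.8% | 93.1% |
| 22 / 35% | 30% | 85.6% | 85.9% | 84.8% |
| 22 / 45% | 35% | 79.1% | 79.9% | 77.3% |
| 15 / 50% | 35% | 78.6% | 81.8% | 79.2% |
| 22 / 55% | 41% | 71.5% | 74.4% | 71.0% |
| 10 / 60% | 39% | 74.6% | 81.6% | 74.3% |

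A second way of rebuilding the 36 subjects gives similar gains: 22/55%, 69.7% to 73.6% (3.9 points); 10/60%, 74.1% to 81.6% (7.5 points). At about 57 per arm, 22/35% stays near 90% with either test, 22/45% goes from 83.0% to 84.0%, and 10/60% from 79.0% to 85.5%.

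**Step 3: where the loss comes from.** At 22/55% the plain test loses 92.5 − 71.5 = 21.0 points relative to 22/22%, and stratifying restores 74.4 − 71.5 = 2.9. At 10/60% it loses 92.5 − 74.6 = 17.9, and stratifying restores 7.0. In every row the single population has about the same power as the pooled mix under the plain test. The fall is therefore due to more deaths that the strategies are assumed not to affect.

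**Step 4: other checks.** If HIV-infected interruptions are also 1.5 times longer, the gain is 2–8 points; if twice as long, 5–15. Type I error of the plain test is 4.9%, 4.6% and 3.7% at 22/22, 22/45 and 10/60%; that of the stratified test is 4.8–4.9%. Using four strata (HIV × initial arm) costs at most about 1 point when nothing differs between strata.

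**The case against.** The strongest reply is that nothing here is wrong. The test is valid, the sample size was simulated with that same test, and an adjusted analysis is already specified, so the dispute is only over which of two planned analyses is primary. The study is ancillary, the protocol itself calls it opportunistic, and it uses a deliberately liberal significance level. The gains rest on mortality values that the document does not supply: 10% for HIV-uninfected patients is less than half the only documented figure (8/36 = 22%). The protocol also does not say whether the 36 source patients included HIV-infected ones; if they did, some of this variation is already in the stated power.

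All of that stands and sets the size of the point. It does not remove the point, because the planned adjusted model is not the primary analysis and the primary result would come from the less efficient test.

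A reader might infer more: that leaving HIV status out of the test forfeits the stated power. The document does not support this. With overall mortality held at 22%, the plain test keeps about 93–94% even when mortality is split 5/35%. Nor is there support for saying that chance imbalance in HIV status distorts the result. That was not tested (the simulations fix the HIV mix in each arm), and imbalance would be limited if each trial randomises its own patients. Nor does the document give evidence that initial arm strongly predicts this endpoint; the efficiency case rests on trial/HIV status.

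**Conclusion.** The point holds as an optional efficiency improvement. The primary DILI test ignores a grouping that the protocol itself shows to be prognostic and the factor used to stratify allocation, but it is valid and consistent with its power calculation. Stratifying by trial/HIV status is worth about 0–4 points of power in most mortality-only scenarios and about 7–8 points at 50 per arm under an extreme 60% versus 10% split. It is worth essentially nothing if overall 60-day mortality stays at 22%. Larger gains, up to about 15 points, need the further assumption that interruptions are twice as long in HIV-infected patients.

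With 22% mortality in HIV-uninfected patients and 50 per arm, power falls below 85% once HIV-infected mortality exceeds about 35%, or sooner if deaths cluster in the first 30 days (78% power at 35% mortality). Stratification recovers only part of that loss. All HIV-specific mortality and duration values are assumptions.

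**What to change.** In Primary endpoint analysis – DILI strategy study, make the primary pairwise comparison a van Elteren (stratified Wilcoxon) test with strata defined by trial (HIV status) and initial randomised arm. Alternatively, promote the planned proportional-odds model with these terms to primary. Keep the unstratified Wilcoxon test as a sensitivity analysis. The sentence should also say which stratum holds TT-genotype participants on open-label dexamethasone, who are eligible for the DILI study but have no randomised initial arm.

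It would help to re-run the power simulation with a stated range of 60-day mortality for HIV-infected patients, since they make up 100/170 = 59% of the expected sample.

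Cost: about one sentence here and the matching sentence in the linked trial's identical ancillary study, because the two are reported together. No new data or patients are needed, and the cost in power is at most about 1 point if the strata turn out not to matter.

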## Inclusion and exclusion criteria

### Inclusion criteria

Study participants for LAST ACT must be adults (aged 18 years or older), HIV-uninfected, with a clinical diagnosis of TBM (≥5 days of meningitis symptoms, and CSF abnormalities) and anti-tuberculosis chemotherapy either planned or started by the attending physician. Participants will be considered eligible for enrolment in this trial if they fulfil all the inclusion criteria and none of the exclusion criteria. The inclusion and exclusion criteria apply at the point of consent, just before the patient’s blood is sent for LTA4H genotyping. Therefore, it is possible that when the LTA4H genotype result returns and the patient is randomised, the patient will have had >3 days of corticosteroids and/or >6 days of anti-tuberculosis treatment. This is acceptable, although the total duration of corticosteroid and anti-tuberculosis treatment before randomisation must be recorded. The time for an LTA4H result to return is not anticipated to be >3 days (e.g. taken on a Friday afternoon and processed on a Monday morning). As TBM is a serious infection requiring hospitalisation, all eligible participants will be treated in hospital, at least for the initial 3 weeks of their illness.

Study participants for the DILI strategy study must be receiving first-line anti-tuberculosis drugs and fulfil the definition of drug-related liver injury: elevation of blood transaminase concentrations ≥3 times the ULN with symptoms and signs of hepatitis (vomiting, abdominal pain, jaundice), or ≥5 times the ULN or a rise in serum bilirubin >2.0mg/dL (>34 µmol/L) without symptoms
^9^, and less than 90 days of anti-tuberculosis drugs given.

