### Trial management

#### Interventions

All participants will receive the standard of care anti-tuberculosis drugs according to national guidelines. Each participant will be LTA4H genotyped. The enrolment and randomisation of the participant into the trial will be finalised according to genotype. TT-genotype participants will be treated with anti-tuberculosis drugs and open label dexamethasone (
Table 2). LTA4H CC- and CT-genotype participants will be randomised to receive dexamethasone or placebo for 6–8 weeks, in addition to anti-tuberculosis drugs, dependent upon disease severity (
Table 2). Study drug will be dispensed at randomisation from the site pharmacy in intravenous and oral (tablet) formulations. Placebo will be identical in appearance to active drug and dosed and dispensed in the same way.

**Table 2. T2:** Study drug treatment regimen following randomisation.

	MRC Grade I Daily dexamethasone dose/route	MRC Grades II and III Daily dexamethasone dose/route
Week 1	0.3 mg/kg/24 hrs IV	0.4 mg/kg/24 hrs IV
Week 2	0.2 mg/kg/24 hrs IV	0.3 mg/kg/24 hrs IV
Week 3	0.1 mg/kg/24 hrs IV	0.2 mg/kg/24 hrs IV
Week 4	3mg/24 hrs oral	0.1 mg/kg/24 hrs IV
Week 5	2mg/24 hrs oral	4 mg/24 hrs oral
Week 6	1 mg/24 hrs oral	3 mg/24 hrs oral
Week 7	Stop	2 mg/24 hrs oral
Week 8		1 mg/24 hrs oral

Participants for the DILI strategy study will be randomised to one of three strategies (
Figure 2): Strategies are as follows:

1)Observe: measure transaminases, bilirubin, and INR every 3 days; do not change/stop anti-tuberculosis drugs unless transaminases rise to ≥10x normal, or total bilirubin rises >2.5mg/dl (>43 µmol/L), or INR >1.5 or symptoms of hepatitis worsen (nausea, vomiting, abdominal pain), in which case go to Strategy 3.2)Stop pyrazinamide alone. Observe, measuring transaminases, bilirubin, and INR every 3 days. If transaminases do not fall to <5x ULN by day 5, or total bilirubin rises >2.5mg/dl (>43 µmol/L), or INR >1.5 or symptoms of hepatitis worsen at any time (nausea, vomiting, abdominal pain), go to Strategy 3.3)Current standard of care (current US CDC guidelines
^9^,
Supplementary File 2).

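### The additional adjusted analysis of the DILI primary endpoint leaves out liver-injury severity at DILI randomisation, so a chance imbalance in it is adjusted for in neither planned analysis

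*Protocol article*

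**What the plan says.** All references are to the protocol article.

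- **Endpoint** (Primary endpoint – DILI strategy study): "the proportion of time in the 60 days following randomisation during which neither rifampicin nor isoniazid are given (or the subject is dead").
- **Primary test** (Primary endpoint analysis – DILI strategy study): "the non-parametric Wilcoxon rank sum test will be used for pairwise comparisons". It has no covariates. The level is a "two-sided significance level of 5% for each of the two primary comparisons of strategies 1 and 2, respectively, versus strategy 3" (Sample size justification – DILI strategy study).
- **Additional adjusted analysis** (same section as the primary test): a proportional odds logistic model "with adjustment for the initial randomisation, HIV-status, and the time from initial randomisation to the second randomisation". The list reads as complete.
- **Entry** (Inclusion criteria): "elevation of blood transaminase concentrations ≥3 times the ULN with symptoms and signs of hepatitis", or a higher transaminase threshold or raised bilirubin without symptoms.
- **Switching** (Interventions): Strategy 1 is to "do not change/stop anti-tuberculosis drugs unless transaminases rise to ≥10x normal", or bilirubin, INR or symptom criteria are met. Strategy 2 moves on if transaminases are not below 5x ULN by day 5, or on the bilirubin, INR or symptom criteria. In both cases the patient goes to Strategy 3.
- **Allocation** (Randomisation): "Randomisation to the three strategies for DILI will be 1:1:1 with stratification by initial randomisation (dexamethasone or placebo"). No liver measure is a stratification factor.

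**The concern.** By the plan's own rules, the liver values at DILI randomisation bear on the outcome. Entry without symptoms starts at 5x ULN and Strategy 1 ends at 10x, so a patient who enters at 9x is much nearer a switch than one who enters at 5x. Under Strategy 2, the patient at 9x must fall by more than 4/9 (44%) within five days to avoid the switch. A patient who enters on symptoms between 3x and 5x is already below that threshold. A switch to Strategy 3 is likely to change the time off rifampicin and isoniazid, which is the endpoint.

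The adjusted analysis is where a reader will look if the arms differ at baseline. If the arms differ in transaminases or bilirubin, the listed model cannot answer the question, and adding those terms after seeing the imbalance would look data-driven.

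The list also has no measure of neurological severity, although days dead count in the endpoint. The main-trial efficacy models do account for MRC grade: the Cox models for the primary endpoint and the models for disability and rescue corticosteroids.

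**Working it through.** **Inputs from the article.** Effect: interruptions under 30 days halved, with longer interruptions and mortality unaffected. Reference data: 36 patients, median interruption 16 days (IQR 12–24), 32 under 30 days, 4 who never restarted, 8 deaths within 60 days. Two-sided 5% Wilcoxon test, at least 50 per arm. Expected total 170, so 170/3 ≈ 57 per arm.

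**Assumed.** The timing of the 8 deaths within the 60 days, and the correlation between baseline severity and the endpoint. The article gives neither.

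**Step 1: the plan's own figure.** The plan says "the power to detect such an effect size with a sample size of at least 50 subjects per arm is >85" per cent. A 36-value pseudo-sample was built to match the stated quartiles, and 4,000 trials were simulated per setting at 50 per arm:

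| Timing of deaths | Wilcoxon power |
|---|---|
| all in days 0–30 | 85% |
| uniform over 60 days | 90% |
| all in days 30–60 | 95% |

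The stated figure is consistent with these. No covariate enters it.

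**Step 2: chance imbalance.** For a standardised baseline measure, the SD of the difference between two arms is sqrt(2/n).

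- n = 50: sqrt(2/50) = 0.200. P(gap > 0.25 SD) = 2 × [1 − Φ(0.25/0.200)] = 2 × [1 − Φ(1.25)] = 21%.
- n = 57: sqrt(2/57) = 0.187. P = 2 × [1 − Φ(1.33)] = 18%.

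The two primary comparisons share Strategy 3, so their gaps have correlation 0.5. The chance that at least one exceeds 0.25 SD is 35% at 50 per arm and 31% at 57.

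**Step 3: what such a gap does.** Expected shift in the outcome = correlation × gap.

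- Correlation 0.36: 0.36 × 0.25 = 0.09 SD.
- Correlation 0.51: 0.51 × 0.25 = 0.13 SD.

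The standard error of the outcome difference is about 0.20 SD at 50 per arm. An effect with 85% power is about (1.96 + 1.04) × 0.20 = 0.60 SD. The shift is therefore about half a standard error (0.45 to 0.65) and about 15% to 21% of the design effect.

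**Step 4: precision gained by adding severity.** Rank ANCOVA at 50 per arm, deaths uniform over 60 days, 3,000 trials per setting:

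| Spearman correlation (assumed) | Without severity | With severity |
|---|---|---|
| 0 | 90% | 90% |
| about 0.2 | 90% | 91% |
| about 0.4 | 90% | 93% |
| about 0.5 | 90% | 96% |

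A second simulation, with a starting power of 85% to 86%, gave 86%, 89%, 90% and 93% at correlations of 0.22, 0.36, 0.44 and 0.51. The gain is thus roughly 1 to 7 points.

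As a cross-check, the normal approximation is power = Φ[(1.96 + 1.04)/sqrt(1 − R²) − 1.96]. From exactly 85%, R² of 5%, 10%, 20% and 30% gives 86.7%, 88.5%, 91.8% and 94.8%. An R² of 20% corresponds to a correlation of 0.45. An R² of 30% corresponds to 0.55, just beyond the range tried.

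**Step 5: type I error.** Under the null it was 4.7–5.0% without severity and 4.6–5.2% with it.

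**The case against.** The strongest reply is that this is a choice within a supportive analysis. The primary comparison is the unadjusted Wilcoxon test, and it meets its power target without covariates. The three listed covariates are reasoned: the stratification factor, HIV status because two trials are pooled, and timing. The study is described as ancillary and opportunistic. All of this stands, and it limits the point to the supportive model.

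A reader might infer that the DILI comparison as a whole loses power or has no protection against imbalance. The documents do not support that. The quoted list does not touch the primary test, and randomisation holds type I error near 5%. What remains is imbalance conditional on the trial that is actually run. At the 0.25 SD gap used here, its effect is about half a standard error, too small to mimic the design effect.

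A reader might also infer that omitting severity biases the odds ratio towards 1. In simulated proportional odds fits the mean log odds ratio did move, from −1.14 to between −1.17 and −1.29. That is largely non-collapsibility: the adjusted model estimates a more conditional quantity.

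Two further points stand in part. The switch rules apply only to Strategies 1 and 2, so severity may act differently by arm, and a main-effects term captures only its average influence. The correlation is also undocumented. Deaths and interruptions that never ended also enter the endpoint, and the article ties neither to liver values at entry.

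**Conclusion.** The point holds as an improvable covariate choice in the additional adjusted analysis. It is neither a contradiction nor a wrong figure. Liver-injury severity is known at DILI entry, governs the move to Strategy 3, is not stratified for, and is absent from the fixed covariate list. A chance imbalance in it, with an 18% to 21% probability of a gap above 0.25 SD per pairwise comparison, would be adjusted for in neither analysis.

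The likely benefit is modest: control of that imbalance, and roughly 1 to 7 power points in the supportive model. The power gain rests on an assumed rank correlation of about 0.2 to 0.5 and on a reconstruction of the 36 reference patients. If severity is not prognostic, the gain is nil. The change is worth making because it needs little and must be prespecified to be credible.

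**What to change.** In Primary endpoint analysis – DILI strategy study, extend the covariate list of the proportional odds model by one sentence, before unblinding. Add log(ALT/ULN), log total bilirubin and presence of hepatitis symptoms, each as measured at DILI randomisation. Add MRC grade at enrolment, because days dead count in the endpoint and 8 of the 36 reference patients (22%) died within 60 days. Keep the three covariates already listed. Leave the Wilcoxon test as the primary analysis, with its level and power statement unchanged.

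The cost is five degrees of freedom (one each for ALT, bilirubin and symptoms, two for a three-level MRC grade) in a model with about 100 to 170 patients. The liver values are needed for entry, and MRC grade is a stratification factor of the main randomisation, so no new data are required here. The linked trial's protocol is not shown, so confirm that it records the same grade. No clinical rule changes.
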